**Unrelated:**

There is not a temporal relationship to investigational product administration (too early, or late, or investigational product not taken), or there is a reasonable causal relationship between non-investigational product, concurrent disease, or circumstance and the AE.

**Unlikely:**

There is a temporal relationship to investigational product administration, but there is not a reasonable causal relationship between the investigational product and the AE.

**Possible:**

There is reasonable causal relationship between the investigational product and the AE. Dechallenge information is lacking or unclear.

**Probable:**

There is a reasonable causal relationship between the investigational product and the AE. The event responds to dechallenge. Rechallenge is not required.

**Definite:**

There is a reasonable causal relationship between the investigational product and the AE.

The **outcome** of all adverse events will be classified as one of the following:

1. On-going
2. Resolved
3. Resolved with sequelae
4. Death
5. Unknown

## 8.6 Solicited Adverse Events and Injection Site Reactions

Solicited AE are events the subject is specifically asked about. These AE are commonly observed soon after receipt of vaccines. For this study, solicited AE to be collected include:

Local: injection site pain, injection site erythema, injection site swelling

Systemic: fatigue, myalgia, arthralgia, pyrexia, chills, nausea.

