### 5.4 Clinical Monitoring

Regular visits performed by the clinical investigators and study nurse will include registration of compliance, adverse events, routine clinical follow-up and examinations (*Mtb* cultures/microscopy/PCR/Gene Xpert, routine blood samples included biochemical parameters associated with organ toxicity, X-ray). S-hCG will be analysed in females to exclude pregnancy (section 6.2.2). Sampling of biobank for primary immunogenicity and exploratory studies according to time-points as stated in section 6.1 (table 1).

In addition, the study nurse will after individual evaluation keep in contact with the participants to secure compliance and safety issues. If there is any question of concern the participants will be seen at an extra visit within few days depending on the issue.

The study arms receiving H56:IC31 vaccine will be monitored for 60 minutes after administration of study vaccine to insure that no acute allergic events are in process and to see if a febrile response is developing. The participants will be examined frequently at time-points as stated in section 6.1 (table 2) to evaluate the physical manifestations of the immunization and with blood samples to assess the biochemical parameters associated with organ toxicity.

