### **6.3.3 Rules for Discontinuing Vaccine Injections in an Individual Subject**

Administration of additional study injections will be discontinued for an individual subject if he/she has any of the following:

- An objective clinical or laboratory parameter change which meets Grade 3 or Grade 4 severity, as defined in the protocol toxicity table, AND is judged to be possibly, probably, or definitely related to study vaccine.
- Fever (oral temperature  $\geq 39^{\circ}\text{C}$ ) within 1 week following study injection which is associated with constitutional symptoms (myalgia, arthralgia, fatigue, headache, anorexia, hives, chills) AND is judged to be possibly, probably, or definitely related to study injection.
- Injection site reaction that involves severe induration ( $>10$  cm, prevents daily activity or necrosis/ulceration), erythema ( $>10$  cm or necrosis/ulceration/ exfoliative dermatitis), tenderness (significant discomfort at rest or study site visit or hospitalization) or pain (any use of narcotic pain reliever or prevents daily activity or study site visit or hospitalization).
- Any event that in the opinion of the principal investigator precludes administration of any further study injections.

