## Visit 6- (day 84)

1. Record any adverse events, including serious adverse events and adverse events of special interest occurring since previous evaluation; record any concomitant medications taken associated with treatment of the adverse event.
2. Focused physical examination by medical practitioner if indicated based on history
3. Vital signs: Blood pressure, pulse, temperature. Weight.
4. Sputum samples
5. **Urine collection:** Confirm continued eligibility for vaccination including negative hcg (urine pregnancy test) for all females of child-bearing potential
6. **Blood collection/number of tubes:**
  - a. Serum chemistry/hematology: **1 EDTA tube (4 ml), 1 serum tube (5 ml).**
  - b. Blood hcg for all females of childbearing potential.
  - c. Biobank: **1 Natrium heparine tube\*(=WHOLE BLOOD), 4 CPT tubes, 1 Pax gene tube.**
7. Anti TB chemotherapy: standard combination therapy. Register any changes in medication in CRF
8. *Vaccine administration study arms #2 and #4:* Confirm subject identification number, check if patient is eligible to receive the study vaccine according to specific criterias. Check subject initials, date and time of dose preparation. Administer study vaccine to deltoid area by intramuscular injection. Record date and time of vaccination and which arm was vaccinated. Monitor subject for acute adverse events for at least 60 minutes after vaccination.
9. Examine site of vaccination 60 +/- 10 minutes post-immunization.
10. Drug dispensing and collecting: Collect and record any excessive study medication and empty medicine containers and if needed: hand out new study medication (Etoricoxib) for study arms #1 and #4. Register in drug accountability log.

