## Visit 7- (day 98)

1. Record any adverse events, including serious adverse events and adverse events of special interest occurring since previous evaluation; record any concomitant medications taken associated with treatment of the adverse event.
2. Focused physical examination by medical practitioner if indicated based on history
3. Vital signs: Blood pressure, pulse, temperature. Weight
4. **Blood collection/number of tubes:**
  - a. Serum chemistry/hematology: **1 EDTA tube (4 ml), 1 serum tube (5 ml).**
  - b. Blood hcg for all females of childbearing potential.
  - c. Biobank: **1 Natrium heparine tube\*(=WHOLE BLOOD), 4 CPT tubes, 1 Pax gene tube.**
5. Anti TB chemotherapy: standard combination therapy. Register any changes in medication in CRF
6. Drug dispensing and collecting: Collect and record any excessive study medication and empty medicine containers and if needed: hand out new study medication (Etoricoxib) for studyarms #1 and #4. Register in drug accountability log.
7. Examine site of vaccination, study arms #2 and #4

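### No temperature, injection-site size or solicited-symptom record is scheduled between the first hour after each H56:IC31 dose and the visit about two weeks later, although the dose-1 stopping criteria and the toxicity table need one

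*Protocol*

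**What the plan says.** **Reactions to be collected.** Protocol section 8.6 introduces solicited events with "Solicited AE are events the subject is specifically asked about". It lists three local terms (pain, erythema, swelling) and six systemic ones: "Systemic: fatigue, myalgia, arthralgia, pyrexia, chills, nausea". It gives no collection days and no recording tool.

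**Early observation.** Section 5.4 says vaccinated participants "will be monitored for 60 minutes after administration of study vaccine to insure that no acute allergic events are in process" and to watch for a developing fever. It continues: "The participants will be examined frequently at time-points as stated in section 6.1 (table 2", which hands the timing over to the flow chart.

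**Schedule.** The flow chart in section 6.1 has no visit between days 84 and 98 or between days 140 and 154. Appendix 6 matches it. On the day of dose 1 (and in the same terms for dose 2) it asks staff to "Examine site of vaccination 60 +/- 10 minutes post-immunization". The next entry is at visit 7: "Examine site of vaccination, study arms #2 and #4", repeated at visit 9. Both of those visits also include vital signs and the instruction "Record any adverse events, including serious adverse events and adverse events of special interest occurring since previous evaluation".

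**What the data must support.** Section 6.3.3 stops further injections for, among other things, an oral temperature of at least 39 °C "within 1 week following study injection which is associated with constitutional symptoms" if judged at least possibly related, and for redness or induration above 10 cm. The toxicity table (Appendix 5) grades fever in half-degree bands at the lower grades, specifies an ear thermometer, and asks for the largest diameter of a local reaction as a continuous value. Section 8.4 says injection-site assessments run over the 14 days after each dose.

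**The concern.** Section 8.6 itself says these reactions tend to appear soon after vaccination, and that is the stretch in which nothing is scheduled. A temperature or a diameter has to be measured on the day. It cannot be reconstructed at a visit two weeks later unless the patient kept a record, and the visit lists neither issue nor collect one.

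Three uses of the data are affected:

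- **The dose-2 decision.** Visit 8 requires staff to confirm that the patient may be vaccinated again, and 6.3.3 makes fever in the week after dose 1 one of the criteria.
- **The Group B safety review.** Sections 3 and 5.10 open enrolment to the combination arm after a review once all Group A participants have completed day 98. That review's dose-1 reactogenicity data consist of the 60-minute check, recall, and whatever is still visible at about day 14.
- **The primary objective.** Section 2 makes safety and tolerability primary, so the grade distribution of early reactions is part of the main result.

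**Working it through.** The protocol gives no figure for this point and no sample-size calculation, so the check is one of schedule arithmetic.

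**Inputs** (flow chart, section 6.1): dose 1 at day 84 ± 7, next visit day 98 ± 3; dose 2 at day 140 ± 7, next visit day 154 ± 3. Fever window in 6.3.3: 7 days after injection.

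**Nominal gap.**
- Dose 1: 98 − 84 = 14 days.
- Dose 2: 154 − 140 = 14 days.
- Scheduled visits in the 7 days after either dose: 0.

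**Windows running from the actual dose date.**
- Earliest visit: 14 − 3 = 11 days. Latest: 14 + 3 = 17 days.
- On this reading the first scheduled temperature after the 60-minute observation always falls outside the 7-day fever window.

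**Windows running from day 0.**
- Earliest, dose 1: (98 − 3) − (84 + 7) = 95 − 91 = 4 days.
- Latest, dose 1: (98 + 3) − (84 − 7) = 101 − 77 = 24 days.
- Dose 2 gives the same: 151 − 147 = 4 and 157 − 133 = 24.
- There are 15 possible dose days and 7 possible visit days, so 15 × 7 = 105 combinations. A gap of 7 days or less needs the dose at least 4 days late and the visit correspondingly early: 4 + 3 + 2 + 1 = 10 combinations. 10/105 = 9.5% if all days were equally likely, which is an assumption. A reading inside the fever window would then occur by chance and not by design.

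**Which criteria depend on measurement.** In 6.3.3, pain and tenderness are defined by function, analgesic use or care sought, and induration has a functional alternative to its 10 cm limit; a patient can report these later. Fever of 39 °C or more cannot be established without a thermometer reading. Redness above 10 cm cannot be established without a measurement, apart from its tissue-damage alternatives. The continuous diameter in the toxicity table also needs a ruler at the time.

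**Where the rule bears.** It governs further injections only, so it matters in the interval after dose 1. Dose 2 is nominally 140 − 84 = 56 days after dose 1 and 140 − 98 = 42 days after visit 7. The gap after dose 2 affects only the safety description.

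**Temperature method.** The fever criterion in 6.3.3 is stated for oral temperature. The first criterion in the same section refers to toxicity grades, and that table uses an ear thermometer. The two passages must be reconciled.

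**The case against.** The case on the other side has real substance.

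- **Collection is scheduled.** A reader might infer that nobody is due to collect these data. That is not so: visits 7 and 9 record all events since the last visit, take vital signs and examine the site, and section 8.6 makes the questions prompted. The supplementary adverse-event tables do list vaccination-site pain and induration, so some reactions reached the record. What stands is that collection is retrospective.
- **Other safeguards exist.** Section 5.4 provides nurse contact after individual evaluation and an extra visit within a few days if there is concern. Section 8 tells patients to call about signs they see as serious. These should catch severe events, but they set no time-point and specify no measurement.
- **The triggers are severe** and more likely to be remembered than mild reactions. This reduces the risk for the dose-2 decision, but it does not supply a temperature that was never taken.
- **The source is incomplete.** The flow-chart footnotes break off at footnote 7, so those attached to vaccine administration and symptoms cannot be read. The Appendix 6 lists for visits 6 to 9 show no diary being handed out or returned. That supports absence in the available text, not proof that none existed.
- **The wording can be read as consistent.** Section 5.4 ties its frequent examinations to the flow chart, and the 14-day period in 8.4 can be read as ending at the next visit. On that reading the sections do not flatly conflict, but early measurements are still not obtained.

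**Conclusion.** The point holds in this form: in the available text, no prospective assessment of temperature, site size or solicited symptoms is scheduled between about 60 minutes after each dose and the next visit. That visit is nominally at 14 days, with a range of 11 to 17 or 4 to 24 days depending on how the windows are anchored. After dose 1, the fever and size criteria of 6.3.3 and the continuous diameter therefore depend on recall or spontaneous report.

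Two stronger readings are tempting and not supported. First, the gap does not show that the vaccine arms are biased toward appearing safe. Patients may forget mild reactions, but the trial is open label without placebo, and prompted recall can also over-report. Second, under-reporting cannot be given a percentage. The documents contain no recall rate, and for vaccine reactions they say only which ones occurred in at least 10% of subjects.

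This is a worthwhile, low-cost improvement to the measurement of a primary objective. It does not invalidate the safety analysis. The conclusion rests on the Appendix 6 visit lists being complete and on the unreadable footnotes adding no contact.

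**What to change.** Reconcile sections 5.4, 6.3.3, 8.4 and 8.6, the flow chart, the toxicity table and Appendix 6, so that the measurements the existing stopping rule presupposes are collected at stated times. State whether the day-98 and day-154 windows run from the actual dose or from day 0. State one temperature method for both the fever criterion and the toxicity grades. Which method is a clinical choice for the sponsor, and no threshold or stopping rule needs to change for this point.

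One practical way is a diary card for arms 2 and 4, issued at visits 6 and 8, covering the 14 days named in 8.4 and collected at visits 7 and 9. It would hold temperature, largest diameter of redness and induration, and the solicited symptoms. Timed telephone contacts with the same items are an alternative.

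The diary costs cards, thermometers and rulers for about 20 patients (10 planned in each of arms 2 and 4), an added data-entry form with some staff time to review it, and a small patient burden. It needs no new visit.

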## 8.7 Reporting Procedure

### 8.7.1 AEs and SAEs

All adverse events and serious adverse events that should be reported as defined in section 8.1.1 will be recorded in the patient's CRF.

SAEs must be reported by the investigator to the sponsor, the medical expert [name], either directly or by phone, within 24 hours after the site has gained knowledge of the SAE. Every SAE must be documented by the investigator on the SAE pages of the CRF. The Serious Adverse Event Report Form must be completed and signed in the eCRF. The medical expert will review the report in the eCRF. The initial report shall promptly be followed by detailed, written reports if necessary. The initial and follow-up reports shall identify the trial subjects by unique code numbers assigned to the latter.

All SAE reports will be collected and communicated annually to the National Regulatory Authority (Norwegian Medicines Agency). SAEs will be recorded if they occurred as follows:

- between the first administration of the study drug and the completion of the last follow-up evaluation, whether or not considered related to the investigational product.
- at any time after completion of the last follow-up evaluation, and came to the investigator's attention and were judged to be related to the subject's participation in the study.

### 8.7.2 SUSARs

SUSARs will be reported to the Norwegian Medicines Agency according to national regulation ("Forskrift om klinisk utprøving av legemidler til mennesker av 30.10.2009 (FOR-2009-10-30-1321)"). The following timelines should be followed:

The sponsor ([name]) will ensure that all relevant information about suspected serious unexpected adverse reactions that are fatal or life-threatening is recorded and reported as soon as possible to the Norwegian Medicines Agency in any case no later than seven (7) days after knowledge by the sponsor of such a case, and that relevant follow-up information is subsequently communicated within an additional eight (8) days.

All other suspected serious unexpected adverse reactions will be reported to the Competent Authority concerned as soon as possible but within a maximum of fifteen (15) days of first knowledge by the sponsor. SUSARs will be reported using in “paper form” or by the the CIOMS form since OUS is not connected to EudraVigilance.

Both SAEs and SUSARs related to the H56:IC31 will be reported to SSI within the same deadlines by cryptic e-mail [[contact]](mailto:[contact]) or fax.nr. [contact].

#### **8.7.3 Annual Safety Report**

Once a year throughout the clinical trial, the sponsor will provide the Competent Authority with an annual safety report. The format will comply with national requirements.

#### **8.7.4 Clinical Study Report**

The adverse events and serious adverse events occurring during the study will be discussed in the safety evaluation part of the Clinical Study Report.

### **8.8 Procedures in Case of Emergency**

The investigator is responsible for assuring that there are procedures and expertise available to cope with emergencies during the study. The study will take place at the outpatient clinic at Dep. of Infectious Diseases, Oslo University Hospital where emergencies can be taken care of during H56:IC31 immunization. When the patient is home he will be given information about telephone numbers to phone in case of emergencies.

## **9 DATA MANAGEMENT AND MONITORING**

### **9.1 Case Report Forms (CRFs)**

The investigator will keep a screening log, recording all subjects who were screened and whether they were enrolled or not. A separate Subject Identification List will be kept, showing code numbers, names, and dates of birth to allow unambiguous identification of each subject included in the study.

The designated investigator staff will enter the data required by the protocol into the electronic Case report forms (CRF). The Principal Investigator is responsible for assuring that data entered into the CRF is complete, accurate, and that entry is performed in a timely manner. The signature of the investigator will attest the accuracy of the data on each CRF. If any assessments are omitted, the reason for such omissions will be noted on the CRFs. Corrections, with the reason for the corrections will also be recorded.

The principal investigator will sign the last page of the CRF. Any corrections to the data will be made in a manner that does not obscure the original entry and will be dated and initialed by the investigator or assigned designee

### **9.2 Source Data**

The medical records for each patient should contain information important for the patient's safety and continued care, and to fulfil the requirement that critical study data should be verifiable.

To achieve this, the medical records of each patient should clearly describe at least:

- That the patient is participating in the study, e.g. by including the enrollment number and the study code or other study identification;

- Date when Informed Consent was obtained from the patient and statement that patient received a copy of the signed and dated Informed Consent;
- Results of all assessments confirming a patient's eligibility for the study;
- Diseases (past and current; both the disease studied and others, as relevant);
- Surgical history, as relevant;
- Treatments withdrawn/withheld due to participation in the study;
- Results of assessments performed during the study;
- Treatments given, changes in treatments during the study and the time points for the changes;
- Visits to the clinic / telephone contacts during the study, including those for study purposes only;
- Non-Serious Adverse Events and Serious Adverse Events (if any) including causality assessments;
- Date of, and reason for, discontinuation from study treatment;
- Date of, and reason for, withdrawal from study;
- Date of death and cause of death, if available;
- Additional information according to local regulations and practice.

### **9.3 Study Monitoring**

The investigator will be visited on a regular basis by the Clinical Study Monitor, who will check the following:

- Informed consent process
- Reporting of adverse events and all other safety data
- Adherence to protocol
- Maintenance of required regulatory documents
- Study Supply accountability
- Facilities and equipment's
- Data completion on the CRFs including source data verification (SDV)

The monitor will review the relevant CRFs for accuracy and completeness and will ask the site staff to adjust any discrepancies as required.

When the responsible study monitor has checked and verified the CRFs, the unidentified data (verified by study code) will be entered into a computer database at the approved scientific server at OUS for further handling and statistical evaluation. The code key will be stored at another approved server.

Sponsor's representatives (e.g. monitors, auditors) and/or competent authorities will be allowed access to source data for source data verification in which case a review of those parts of the hospital records relevant to the study may be required.

## **9.4 Confidentiality and database management**

All information concerning the study will be stored in a safe place inaccessible to unauthorized personnel. The entry of data and coding will be secured by two study nurses. The following information will be retained at the investigator's site for at least 15 years after final patient visit according to "Forskrift om klinisk utprøving av legemidler til mennesker av 30.10.2009 (FOR-2009-10-30-1321)".

- Source documents
- CRFs
- Copies of protocols
- Protocol amendments
- Drug accountability forms
- Correspondence
- Subject identification lists
- Informed consent forms
- Copies of study reports

## **10 STATISTICAL METHODS AND DATA ANALYSIS**

### **10.1 Determination of Sample Size**

This is a first of its kind exploratory open label phase I study. Primary efficacy data of COX-2i as well as the H56:IC31 vaccine in patients with active TB are non-existing. Further, it is not optimal to extrapolate efficacy data from H56:IC31 studies of latent TB patients. Thus, a sample size calculation is therefore not performed. Still, H56:IC31 studies have shown significant differences in vaccine immunogenicity with 10 patients in each arm and we have proven differences in immune activation (CD38) in a HIV cohort after 12 weeks on high dose celecoxib (Pettersen et al., 2010) with 13 and 14 patients in the study and control groups, respectively.

